##### Family activities

Will be toward to parents and include health education activities for parents, as well as supervision and encouraging children and adolescents to increase their levels of physical activity outside of school. Table 4 for details.

**Table 4 Tab4:** Interventions for students

Intervention Concept	Interventions
2 (2 h daytime outdoor activities)	1. Go out of the classroom between classes and actively participate in large recess activities
	2. Put some indoor activities outdoors during the day, and actively participate in daytime outdoor sports interest groups
	3. Walk to school, set up a school group with classmates (“healthy school bus”), delineate the route for students to walk to and from school, and parents pick up and drop off children at specific times and specific stops
	4. Complete the homework assigned by the school for daytime outdoor activities, such as adhering to daytime outdoor physical activity for more than 2 h on rest days
2 (Limit screen time to no more than 2 h per day)	5. The single use of entertainment electronic products should not exceed 15 min, and the cumulative use of electronic products should not exceed 1 h per day. After 30–40 min of learning with electronic products, you should take a break and relax for 10 min. The younger you are, the shorter you should continue to use electronic products
	6. Avoid bad screen habits, do not use electronic products in dimly lit environments, and avoid using electronic products in a lying position and before going to bed
	7. When viewing the screen, the shoulders should be kept relaxed, the upper back should be extended, the upper arm should be at 90° to the forearm, the wrist should be relaxed, and breathing regularly
	8. When writing homework, keep your eyes about one foot away from the book (about 30 cm), your body about one punch (about 6 cm) away from the desk, and your fingers about one inch (about 3 cm) away from the tip of the pen
5 (Consume at least 5 servings of fruits and vegetables daily), 1 (Attain 1 h of physical activity daily) and 0 (Consume 0 sugar-sweetened beverages)	9. Take health education courses on dietary nutrition and develop a reasonable diet and healthy living habits
	10. Learn about food nutrition labels and choose food reasonably
	11. You should maintain balanced nutrition, not picky eaters, not partial eclipse, not overeat, and eat more fresh vegetables and fruits
S (Reasonable sleep duration)	12. Students should kept enough sleep every day. It was recommended that pupils should not be less than 10 h and junior middle school students should not be less than 9 h
	13. Avoid going to bed late and getting up late on an irregular schedule

##### School activities

Will included school policies related to the prevention of myopia and obesity and health education activities for teachers. Table 5 for details.

**Table 5 Tab5:** Interventions for schools

Intervention Concept	Interventions
2 (2 h daytime outdoor activities)	1. Parents should create a family atmosphere of physical activity for children, and allow children to spend 1 h outside school every day
	2. Encourage students to walk or accompany children to school on foot
	3. Parents regularly monitor children’s growth and development, measure height, weight, and waist circumference at least every three months, and keep records
	4. Spend more time on weekends and holidays to participate in daily outdoor activities with children, walk into nature, and get close to the sun
2 (Limit screen time to no more than 2 h per day)	5. Control the time that children use electronic products. The daily entertainment video time should not exceed 20 min each time, and the total time should not exceed 1 h. Younger children and teens should have less screen time for entertainment
	6. Parents should regularly monitor their children’s vision. If they find that their children squint, rub their eyes frequently, or look at the text on the blackboard or objects in the distance that is unclear in class, they should consider the possibility of myopia and take their children to the hospital in time
	7. Instruct children to develop good eye habits, improve children's awareness of eye care and eye protection, instruct children to develop good eye habits, and avoid using eyes at close range for a long time
	8. Guide children to develop the habit of resting between their eyes for a long time, especially resting their eyes through exercise
5 (Consume at least 5 servings of fruits and vegetables daily), 1 (Attain 1 h of physical activity daily), and 0 (Consume 0 sugar-sweetened beverages)	9. Buy food as needed, choose fresh and hygienic food, and store it reasonably
	10. Learn about food nutrition labels, pay attention to food labels when purchasing food, and choose healthy food for students
	11. Parents provide students with small portions and a variety of food, encourage them to eat more vegetables, fruits, and high-quality protein at home, eat fewer sweets, and not drink sugar-sweetened beverages. Ensure regular meal times, meal locations, and appropriate eating or serving utensils. Supervise to help students eat slowly, not picky eaters, not partial eclipse
S (Reasonable sleep duration)	12. Implement appropriate restrictions on students’ use of electronic products before bedtime
	13. Lead by example, consciously maintain a good routine, let students recognize the importance of sleep, and develop a good habit of independently maintaining a routine

##### WeChat applet

Will be provided to project team, clinic doctors, school teachers, and parents to follow. The applet will develope corresponding application modules based on behavior change technology. Assistance will be provided in information dissemination, behavioral supervision, weight management, assessment, and feedback. Table 6 for details.

**Table 6 Tab6:** Interventions for parents

Intervention Concept	Interventions
2 (2 h daytime outdoor activities)	1. Under the guidance of the teacher, let each student master 1–2 physical skills
	2. Improve the school environment, increase the large class time in the morning and afternoon (one in the morning and one in the afternoon, 30 min each time), and encourage all teachers and students to participate in daytime outdoor activities together
	3. Encourage students to go out of the classroom between classes. The lower-grade students can be led by teachers to play some group games, etc.;
	4. Guarantee the school physical education class and the big break time: the school should try to avoid the phenomenon of physical education class being occupied or suspended, and if the weather is bad, it should organize students to exercise in indoor venues
2 (Limit screen time to no more than 2 h per day)	5. Control the teaching time of using electronic products in schools, in principle, it does not exceed 30% of the total teaching time
	6. Teach children the knowledge and skills of weight control and myopia prevention through classroom lectures, visits and demonstrations, face-to-face tutoring, and group activities
5 (Consume at least 5 servings of fruits and vegetables daily), 1 (Attain 1 h of physical activity daily), and 0 (Consume 0 sugar-sweetened beverages)	7. School canteens or catering companies provide students with food that is nutritionally balanced, reasonably cooked, and in line with local dietary characteristics, provide nutrition labels for catering food, and feedback on the appropriate recipes to parents
	8. In the whole school, the school canteen, commissary, vending machine, and other places eliminate the supply of unhealthy food such as sugar-sweetened beverages, potato chips, and sweets; unhealthy foods such as sugar-sweetened beverages, potato chips, and sweets are not allowed in the school. Educate students not to buy unhealthy foods such as sugary drinks, potato chips, and sweets at school gates
	9. Regularly post health education posters and improve school food environment signs on the notice board on campus and in the classrooms of participating classes
S (Reasonable sleep duration)	10. Establish reasonable school hours for students
	11. Reduce the burden of homework after school, and do not let too many academic tasks crowd out students' sleep time

#### Control group

The children and adolescents in the control schools will have only regular monitoring and class meetings or health education classeswithout clinic doctors’ paricipating.

### Quality control of the intervention

Two manuals have been developed to facilitate the implementation and management of this complicated intervention. These manuals include the “Operation Manual for Intervention Project Team members” and the “Operation Manual for Intervention School Team Members”. The manuals provide the specific technologies, frequency, and duration of the intervention, as well as a checklist to ensure that the intervention is implemented as required. The manuals also outline the training and responsibilities of each delivery person involved in the project, such as project members, school principals, school doctors, health teachers, physical education teachers, as well as children and adolescents. Additionally, the manuals provide detailed instructions regarding the responsibilities and division of labor of project team and school team members, for the implementation of intervention measures. They also describe the workflow for each intervention content, outlining who, when, how, and to what extent the specific intervention content should be delivered. All project team and school team members are expected to adhere to the operational manuals in the delivery of intervention. The intervention implementation process will be monitored regularly, and feedback will be provided by project team in a timely manner.

### Data collection

#### Qualitative data collection

##### Expert interview

Has been conducted by individual interview or focus group for intervention package development and format “22510SS”. The experts and scholars are senior and experinced in the field of child and adolescent health. The interviews has been organized by trained investigators.

##### Delphi study

Has been conducted with 20 experts from various fields, including ophthalmology, endocrinology, pediatrics, school health, school sports, health education, and stakeholders with extensive experience in the prevention and control of children’s myopia or obesity. The study has carried out three rounds of expert consultation to determine intervention package and make the priority order of intervention package via email.

#### Quantitative data collection

In March 2023, we will conduct baseline data collection and assessments for both the intervention and control groups. Throughout the 12-month intervention period, we will conduct periodic follow-up assessments as outlined in Table 7. Anthropometric data, biospecimen data, and environmental measurements will be collected at baseline and at follow-up at the end of the intervention. All measurements will be taken uniformly trained and qualified staff and collected by investigators using the same equipment and/or forms by standard methods and procedures. Investigators who measure children and adolescents’ visual acuity, refraction, height, and weight will be blind to the information of intervention or control group. Table 8 shows a trial participant timeline.

**Table 7 Tab7:** Interventions for schools

Intervention Concept	Interventions
S (Regular supervision)	1. The project team regularly disseminates the relevant knowledge of the project’s health education activities to students, parents, and teachers through the mobile WeChat official account
	2. Parents and students fill in a health behavior questionnaire on a regular basis through the WeChat official account of the mobile phone. The project team and the school can learn about the health behavior of students through the official account
	3. The project team will automatically generate comprehensive evaluation results based on the student's physical examination information and WeChat official account
	4. The project team uses the mobile phone WeChat official account to dynamically monitor the vision, height, and weight of all students participating in the project. The mobile phone WeChat official account automatically provides encouragement or guidance to students, parents, teachers, and the project team
	5. Parents upload the student's physical examination or weight monitoring information every three months to the mobile WeChat public account. The mobile WeChat public account will provide health prescriptions issued by experts from Beijing Children’s Hospital Affiliated with Capital Medical University, and provide information on intervention and treatment. Timely feedback is provided to individual families and schools, and intervention prescriptions are jointly implemented by home schools and the community

**Table 8 Tab8:** Contents of the baseline survey and secondary follow-up survey

Measurement indicators	Baseline survey	3 month follow up	12 month follow up	Method

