	**STUDY PERIOD**			
	**Enrollment**	**Allocation**	**Post-allocation**	**Close-out**
Time point	September–October 2022	October 2022- April 2023	June-July 2023	November–December 2023

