**Enrollment**				
Eligibility screen	X			
Informed consent	X			
Allocation (cluster)		X		

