**Interventions**				
Intervention		X		
Control		X		

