## Discussion

This study aimed to develop a comprehensive intervention strategy “22510SS”, to combat the prevalence of myopia and obesity among children and adolescents, guided by a SEM and evidence-based interventions. The strategy involved interventions in individual, family, school, community, and clinic, and its effectiveness and implementation will be evaluated within the RE-AIM framework. If the study works, it will be embeded into the regional monitoring system in Beijing, to promote the development and evaluation of comorbities prevention services for children and adolescents, and promote the establishment of a healthy and friendly environment system for children and adolescents.

Although there have been numerous individual intervention studies on myopia and obesity in children and adolescents, there is currently no comprehensive intervention plan addressing both conditions. Our project team has optimized and integrated key technologies developed in the early stages to prevent myopia and obesity in children and adolescents, and apply these technologies in the Dongcheng, Tongzhou, and Changping districts of Beijing through pre-testing. This enables us to develop an evidence-based intervention of “22510SS” to use in this trial.

Despite the factors influencing myopia and obesity in children and adolescents are complex, they are primarily distributed across individual, family, school, community levels, and clinics [55, 56]. Previous intervention studies have mostly focused on school or family-based approaches, while ignoring the impact of community and medical institution interventions on children and adolescents with myopia and obesity [57, 58]. The development and assessment of interventions targeting myopia and obesity have been carried out through expert workshops and expert letters, followed by pre-surveys involving 300 participants across 18 intervention schools. The interventions were designed to bring about change at multiple levels, including children and adolescents, families, schools, communities, and healthcare organizations.

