Previous intervention studies have demonstrated satisfactory short-term intervention effects, but maintaining long-term and repeatable effects has been a challenge due to the termination of intervention projects. To address this, our study established an evaluation model based on the RE-AIM framework, which evaluates the feasibility, sustainability, fairness, potential impact, acceptability, health economics, and health economics of the intervention model in the demonstration area [60]. This continuous evaluation promotes the sustainability of intervention effectiveness and enables policies and interventions to be constantly improved and developed. Moreover, the experience of the demonstration area has been extended to all primary and secondary schools in Beijing through the “National Monitoring of Common Diseases and Health Influential Factors of Children and adolescents” system, increasing the influence of the intervention measures and the durability of their effects. Our approach can provide a valuable framework for promoting the long-term effectiveness of existing interventions and improving the health outcomes of school-aged children.

This study has several notable strengths. First, it represents the first comprehensive intervention in China aimed at reducing the risk of two common diseases in children and adolescents: myopia and obesity. The intervention strategy, known as “22510SS”, draws on the social-ecological model (SEM) and considers the roles of individuals, families, schools, communities, and healthcare providers for optimal efficacy. Second, the study will use a RE-AIM-based framework to evaluate the intervention strategy and implementation outcomes.While this study is expected to make significant strides in reducing the risk of myopia and obesity in children and adolescents, there are potential limitations to consider. For example, the study will only recruit volunteers from three districts in Beijing, which may not be representative of all Beijing children and adolescents, let alone the entire population of China. Furthermore, as a hybrid design implementation study, some of the results will be assessed primarily through qualitative interviews. Therefore, the feasibility, acceptability, and sustainability of the intervention in practice may not be fully represented. As a result, the generalizability of the study's findings may be limited.

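### The March 2023 baseline cannot be reconciled with Table 1's dates, a 12-month intervention and a 12-month primary endpoint

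*Protocol article*

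**What the plan says.** The article gives two dates for the first measurement.

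- **Text, Quantitative data collection:** "In March 2023, we will conduct baseline data collection and assessments for both the intervention and control groups".
- **Table 1 (participant timeline):** enrolment is "September–October 2022", and the only marks for anthropometric measures and the questionnaire stand in that column. Cluster allocation, intervention and control are all marked in the next column, "October 2022- April 2023". The post-allocation column is June–July 2023 and close-out is November–December 2023.

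Three other statements depend on these dates. Study design gives a 12-month intervention. Primary outcome defines change in visual acuity and body mass index 12 months after baseline. Table 8 schedules follow-up at 3 and 12 months. Statistical analyses compares the changes with a mixed-effects model that accounts for school, and adds a difference-in-difference analysis.

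The Discussion has two further remarks. It reports "pre-surveys involving 300 participants across 18 intervention schools". It also says that "the experience of the demonstration area has been extended to all primary and secondary schools in Beijing", although earlier in the same section the step is conditional: "If the study works, it will be embeded into the regional monitoring system in Beijing". The Control group section limits control schools to regular monitoring and class meetings or health education classes, without clinic doctors.

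**The concern.** Change from baseline means something only if baseline comes before the intervention and the endpoint comes at the stated distance after it. March 2023 lies inside the window that Table 1 gives to allocation and intervention, so on the printed dates neither condition is secure.

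Two consequences are possible. If delivery began before baseline, part of any effect may already be in the baseline value, and both the change score and the difference-in-difference would subtract it. If allocation was disclosed before baseline, the questionnaire items are exposed. The blinding statement covers only the staff who measure visual acuity, refraction, height and weight. Questionnaires are completed with parental help in grades 1–4 and class-teacher guidance in grade 7, and those people may know the school's arm. The behavioural measures listed under the primary outcome come from these questionnaires.

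**Working it through.** The check is a count of calendar months.

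**Inputs:** baseline March 2023 (Quantitative data collection); enrolment September–October 2022, allocation and intervention October 2022–April 2023, post-allocation visit June–July 2023, close-out November–December 2023 (all Table 1); intervention length 12 months (Study design); endpoint 12 months after baseline (Primary outcome); visits at 3 and 12 months (Table 8).

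**Step 1. Test each candidate baseline against the visits.**

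| | Baseline March 2023 | Baseline September–October 2022 |
|---|---|---|
| Position relative to October 2022, when the allocation window opens | 5 months after | 1 month before to same month |
| Months to June–July 2023 | 3–4 | 8–10 |
| Months to November–December 2023 | 8–9 | 13–15 |
| Date 12 months after baseline | March 2024 | September–October 2023 |

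March 2023 fits the 3-month visit but misses the 12-month visit by 3 to 4 months. The enrolment date fits neither exactly: the first follow-up comes far too late for a 3-month visit, and close-out is 1 to 3 months beyond 12.

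**Step 2. Place the intervention.** Twelve months before November–December 2023 is November–December 2022. From there to March 2023 is 4 or 3 months. A 12-month intervention finished by close-out therefore starts 3 to 4 months before a March 2023 baseline. If delivery instead starts at or after March 2023, twelve months end in March 2024 or later, which is 3 to 4 months after close-out.

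**Step 3. Read Table 1's intervention mark literally.** October 2022 to April 2023 is seven calendar months, counting both ends. A 12-month intervention does not fit in it, so the mark cannot give the whole delivery period.

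**Result.** The March 2023 baseline, the 12-month intervention, the 12-month endpoint and the Table 1 close-out cannot all be true. Keeping the first and the last means either a baseline after first delivery or less than 12 months of intervention, and in both cases an endpoint at 8 to 9 months.

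**The case against.** The strongest reply is that no late baseline has been shown. Table 1 places measurements at enrolment, before or at the opening of the allocation window, so one of the two printed dates is in the right order. No section gives the date of first delivery. The allocation window is wide enough for delivery to begin after March 2023, and June–July 2023 then fits the 3-month visit. This stands: the defect is an unresolved contradiction. It does not remove the defect, because that reading contradicts either the 12-month length or the close-out date (Step 2).

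Several stronger readings are tempting, and the documents do not support them.

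- **That the effect is diluted by a known share**, for instance five months out of twelve. This needs delivery from October 2022, linear build-up, and exposure that ends at month 12. None is stated. If delivery continued until 12 months after baseline, linear build-up would imply no loss. The 90% power in the Sample size section belongs to a co-morbidity proportion, so it gives no power loss for visual acuity or body mass index.
- **That the pre-surveyed pupils were already exposed and should be excluded.** The article does not say that these 300 received the package or will be enrolled, and dropping them would remove pupils from one arm only. The pre-survey suggests only that the intervention schools were identified early.
- **That control schools have already received the package.** The remark on extension is undated, speaks of experience passed on through a monitoring system, and does not mention control schools.
- **That all outcomes suffer from unblinded measurement.** Those who measure vision, height and weight are stated to be blinded.

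**Conclusion.** The point holds as a contradiction of dates with a real consequence for the primary analysis. On the printed dates, a March 2023 baseline leaves 8 to 9 months to close-out against a required 12, and a 12-month intervention finished by close-out would begin 3 to 4 months before that baseline. These figures rest only on calendar arithmetic.

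Bias is conditional. If delivery or disclosure preceded baseline, the change-from-baseline and difference-in-difference estimates may be biased towards no effect, and questionnaire baselines may be affected in a direction that cannot be stated. The documents give neither the start of delivery nor the time of disclosure, so no size can be derived.

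The tension between the reported and the conditional city-wide extension is secondary: it leaves the control condition unclear but does not show contamination.

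**What to change.** 1. Reconcile Study design, Table 1, Quantitative data collection and Primary outcome by stating one baseline. It should be complete in all 36 schools before allocation is disclosed to any school and before first delivery. State the dates of disclosure and first delivery beside it.
2. Correct Table 1 so that the final measurement falls 12 months after that baseline.
3. If measurement has already taken place, which is possible because the article is dated July 2023, use the September–October 2022 enrolment measurements as the analysis baseline where they exist, in both arms alike. Report the true interval to the final visit: 13–15 months if close-out stays in November–December 2023.
4. Reconcile the Discussion's statement on extension with its conditional statement and with the Control group section, by stating that no part of the package reaches the 18 control schools before their 12-month measurement.

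**Cost.** Items 1 and 4 are corrections of text, unless extension to control schools is already under way and has to be delayed. If March 2023 is the true baseline, item 2 moves the final visit from November–December 2023 to March 2024, a delay of 3 to 4 months. Item 3 needs no new measurement, but it depends on how complete the enrolment data are.
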